## Abstract

**Background:**

Studies have shown that functional strength and balance exercises can reduce the risk of falling in older people if they are done on a regular basis. However, the repetitive nature of these exercises; combined with the inherent lack of feedback of progress may discourage seniors from exercising in the home, thereby rendering such an intervention ineffective. This study hypothesizes that the use of visual feedback and multimodal games will be more effective in encouraging adherence to home rehabilitation than standard care; thereby promoting independence and improving the quality of life in older adults at risk of falling.

**Methods:**

A pllel-group pilot randomized controlled trial with 3 groups of participants will be conducted in the home for 12 weeks. Participants will include older adults who have been identified as at risk of falling (n = 48), over the age of 65, living in the community, and suitable for a home exercise intervention. The primary outcome is adherence to exercise. Secondary outcomes include: variability in stride length, stride time and double support time (DST); walking speed; Timed up and go test (TUG); Falls Efficacy Scale International (FES-I); CONFbal scale; Romberg’s test; and quality of life measures (SF-12 and EuroQol EQ-5D). Qualitative assessments on personal experiences with rehabilitation tools will be done before and after the trial.

**Discussion:**

This study will investigate the use of visual feedback and engaging multimodal activities to address the problem of non-compliance to home exercises for falls rehabilitation. One of the unique qualities of this study is the adaptation of special participatory design methods through which the end users (fallers) will be involved in the design of the proposed rehabilitation tools at various stages of the design process.

**Trial registration:**

ISRCTN79967470

## Background

### Falls and adherence to exercise

Thirty percent of people over the age of 65 years fall at least once a year
[1], with over 75% of this population suffering an injury as a result. Fractures (a major consequence of falls) alone cost the National Health Service (NHS) in the UK about £1.8 billion
[2]. Although falls can be caused by a wide variety of factors (including visual and physical impairment), many cases are attributed to a lack of exercise as well as weaknesses in muscles, bones and joints in the lower body
[3]. These conditions can be improved by rehabilitation designed to improve the patient’s ability to cope with movement in everyday life, increase the patient’s functional capacity, elevate confidence and reduce the fear of falling
[4].

Evidence has shown that certain rehabilitation exercises such as the Otago exercise program and Falls Management Exercise (FaME) are effective in returning falls patients to normal functional movement if the patient adheres to the routine
[5]. However, there is an existing problem with adherence to these exercises, which could be attributed to a wide variety of factors, such as low confidence in the rehabilitation programme and lack of motivation on the user’s part
[6]. In the home, motivation to exercise can also be affected by the somewhat repetitive nature of the current exercises and the way that they are presented to the user (through paper-based illustrations), which could make the rehabilitation process seem like a chore for the patient
[7,8].

To address this problem of low adherence to home exercises, it is necessary to first identify the common problems that fallers face in the home, and what effects these problems may have on seniors’ confidence, fear of falling, and quality of life. Furthermore, it is essential to explore the limitations of standard rehabilitation care in order to determine how these limitations may affect their adherence to home rehabilitation programmes. In this study, there is an investigation into how visualizations and games could be used to encourage greater participation in home rehabilitation.

### Visual feedback of activity

In the past, visualizations of movement have been explored by Macdonald *et al*.
[9] to promote engagement in rehabilitation. The theory behind this study suggested that if the seniors were more involved in their rehabilitation, they could take greater steps to ensure that they became more independent. This study involved testing gait in the lower limbs, while providing visualizations of the exercise using a motion capture system. The results showed that the simple visualizations (which consisted of a stick figure on a screen using a traffic light system - green, amber and red - to show varying levels of stress in joints during activity at different times) were able to bridge the gap in the understanding of important data between the patient, clinicians, biomechanists and physiotherapists. By doing this, the seniors felt more involved because a discussion could be had between them and the therapists on how best to facilitate their recovery. In a similar vein, the study by Yavuzer *et al*.
[10] revealed how the use of visual feedback through balance training, in addition to a conventional stroke rehabilitation programme, improved postural control and weight-bearing in late-stage stroke patients. One of the limitations of these studies is that factors such as equipment size, cost, and the complex setup involved means that the experiments need to be restricted to the clinical, or laboratory setting.

Virtual environments and video games have also proved successful in providing an engaging rehabilitation experience for patients with a wide variety of ailments, including stroke and chronic obstructive pulmonary disease (COPD)
[11,12]. The use of commercially available games such as Wii-Fit has become a staple of encouraging physical activity in older adults, mostly in the clinical setting
[13,14]. However, rehabilitation often involves specifically tailored exercises that promote the recovery of muscle groups necessary for improved strength, balance and mobility. Therefore, there is a need to go one step further in the design of games, in order to make them useful for rehabilitation purposes. It is believed that an efficient way to tackle this problem is to design games that encourage limb movements that are characteristic of rehabilitation, in order to promote effective recovery of muscle strength and balance.

In one arm of the study described in this paper, we will explore how visualizations of movement may be used to encourage older adults at risk of falling, to exercise in the home. The main aim of the visualizations in this study will be to advise users on the most efficient way to perform each exercise. Using simple body-worn sensors, the users’ body movements can be tracked, and the information from these sensors can be used to inform the users on simple biomechanical concepts that are useful to their rehabilitation, such as joint angles and range of motion.

To tackle the ever-present problem of the lack of interest and adherence to the rehabilitation routine, this study also aims to employ the use of multimodal games, based on rehabilitation exercises, which will enable users to perform exercises in an enjoyable manner and hence provide a suitable opportunity for effective functional recovery. To maximize the potential of the use of games for this purpose, older adults have been involved at various stages of the design process, including the initial concept design stage, in order to address the main issues that they may face, through the use of these tools in a realistic unsupervised home setting
[8]. It is anticipated that by using games to exercise, the repetitive movements necessary for rehabilitation can be made more enjoyable for the user, which should have a positive effect on confidence and adherence to the exercise programmes in the home.

## Methods/design

### Research questions

1. Can visual feedback of movement during home exercise improve adherence to falls rehabilitation programmes?

2. Can the use of multimodal games for falls rehabilitation in the home improve adherence to exercise?

### Study design

The study will involve a three-arm, pllel-group randomized controlled trial (RCT) based in the community. Participants will provide written informed consent prior to taking part in the study. Randomization will be done using a computer-based number generator. Participants in all three groups will be allocated an intervention based on a 1:1:1 ratio (Figure
1). The trial will be carried out over a 12-week period.

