### Participants

Participants who have had injurious falls will be recruited from the NHS Greater Glasgow and Clyde community falls prevention programme (CFPP). Participants who have had non-injurious falls will be recruited from the Glasgow Housing Association Sheltered Housing Scheme. Recruitment will occur at the point where older adults at risk of falling are offered home exercise by the physiotherapists at the CFPP, who will hand out information sheets and explain the study to the potential participants. Interested participants who meet the inclusion criteria and have given informed consent will then be randomized into one of the groups involved in the trial.

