### Sample size

This study is a pilot RCT and as such, no power calculation has been carried out. It is intended that the results obtained from this study will inform the design of a larger trial upon which a robust power calculation can be done based on adherence to exercise.

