### Statistical analysis

For qualitative data, Likert scales will be used for some questions, and for the open-ended questions, thematic coding will be used. Quantitative data from the laboratory tests (baseline and outcome measures of gait and balance) will be analysed on an intention-to-treat basis. Statistical analyses will focus on the possible existence of differences in outcomes between the control and intervention groups using a two-way, repeated-measures analysis of variance (ANOVA).

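### Recruitment source is tied by design to fall severity, but is named neither as a randomization factor nor as a term in the analysis

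*Protocol article*

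**What the plan says.** The Participants section of the protocol article sets up two recruitment streams: "Participants who have had injurious falls will be recruited from the NHS Greater Glasgow and Clyde community falls prevention programme (CFPP"), and "Participants who have had non-injurious falls will be recruited from the Glasgow Housing Association Sheltered Housing Scheme". It then describes a single randomization step for everyone: "Interested participants who meet the inclusion criteria and have given informed consent will then be randomized into one of the groups involved in the trial".

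The Study design section describes the allocation in two sentences: "Randomization will be done using a computer-based number generator" and "Participants in all three groups will be allocated an intervention based on a 1:1:1 ratio". Neither sentence mentions stratification, blocking or minimization.

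The abstract gives the size, "older adults who have been identified as at risk of falling (n = 48"). The Sample size section adds "This study is a pilot RCT and as such, no power calculation has been carried out" and says that the results are to inform a larger trial, powered on adherence. The Statistical analysis section compares control and intervention groups "using a two-way, repeated-measures analysis of variance (ANOVA"). The natural reading of the two factors is group and time. Recruitment source is not mentioned.

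**The concern.** The trial draws on two populations that it separates by fall severity. A previous injurious fall could plausibly affect confidence, fear of falling, gait and willingness to exercise, which are the things the trial measures. The article gives no figure for any such link. With about 16 per arm, chance can leave the arms with noticeably different mixes of the two sources.

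Two things are at stake. First, an observed difference between arms may partly reflect a difference in source mix, and a pilot this small has little information with which to separate the two. Second, variation between sources that is left in the error term widens the intervals and inflates the standard deviation available for the later power calculation. Source is known for every participant at entry, so leaving it out of allocation and analysis gives up an easy gain.

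**Working it through.** The plan states no imbalance or power figure to reproduce. The only stated quantities are n = 48 (abstract) and the 1:1:1 ratio (Study design), which give 48/3 = 16 per arm.

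**Assumptions not in the documents.** The split of the 48 between sources is taken as 24/24, 32/16 or 36/12. Which source is the larger does not change the result. A gap of 25 percentage points in source share is taken as material; with 16 per arm that is 4 participants. All figures below apply only if allocation is not stratified by source.

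**Arms fixed at 16/16/16.** Let *m* participants come from one source, with *a* and *b* in the two intervention arms and *c* in control. Then

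P(a, b, c) = C(16,a) × C(16,b) × C(16,c) / C(48,m).

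This is summed over |a − c| ≥ 4 or |b − c| ≥ 4.

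**Simple randomization, probability 1/3 per arm.** Each source's counts are an independent multinomial. The probability is summed over outcomes where either intervention arm's source share differs from control's by at least 0.25.

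| Source split | At least one intervention-versus-control gap ≥ 25 points: arms fixed | Same: simple | One given pair: arms fixed | Same: simple |
|---|---|---|---|---|
| 24/24 | 36% | 29% | 22% | 17% |
| 32/16 | 33% | 26% | 19% | 15% |
| 36/12 | 26% | 21% | 16% | 12% |

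Counting any pair of arms, including the two interventions against each other, gives 43% (fixed) and 36% (simple) at 24/24, and 32% and 26% at 36/12.

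**What a 25-point gap does to an estimate.** The documents give no effect of source on any outcome, so this is an illustration. If source shifts an outcome by δ within-source standard deviations, a gap of 0.25 moves the arm difference by 0.25δ. The standard error of a difference between two arms of 16 is √(1/16 + 1/16) = 0.354 SD.
- δ = 0.5: shift 0.25 × 0.5 = 0.125 SD, and 0.125/0.354 = 0.35 of a standard error.
- δ = 0.8: shift 0.25 × 0.8 = 0.20 SD, and 0.20/0.354 = 0.57 of a standard error.
- δ = 0: no shift.

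**Effect on the variance carried forward.** At an even split, leaving source out adds 0.5 × 0.5 × δ² to the variance. This gives 1 + 0.25 × 0.25 = 1.06 for δ = 0.5, and 1 + 0.25 × 0.64 = 1.16 for δ = 0.8.

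**After the fix.** With permuted blocks within source and source totals that fill whole blocks (24/24 or 36/12), each source divides equally over the arms and the gap is 0. An incomplete last block leaves a difference of at most one participant per source with blocks of 3, and two with blocks of 6.

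**The case against.** The strongest objection is that the article never calls allocation unstratified. It is a condensed account, and strata, block sizes and covariates may be set out in a fuller protocol or analysis plan. This stands in part. A reader might infer an unstratified scheme, but that would be reading silence as a statement, so every probability above is conditional. The objection does not remove the point. The article itself builds in the two populations, pools them in one randomization step and names an analysis without source; adding source improves the method as stated.

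Three other stronger readings are not supported.
- *A number generator cannot deliver 1:1:1.* A computer generator is also how blocked and stratified lists are made, and the stated ratio is compatible with blocking.
- *Imbalance is likely.* For comparisons with control, every figure in the table is below one half, and for a single pair the highest is 22%.
- *Source is fully tied to housing type and to contact with the falls service.* The text ties source to injurious versus non-injurious falls only. It does not state the housing of programme participants, and it places recruitment at the point where programme physiotherapists offer home exercise.

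It is also fair to say that chance imbalance does not bias a randomized comparison in expectation, that the shift illustrated is a fraction of a standard error, and that measuring gait and balance at baseline and at the end partly absorbs starting differences. All of this stands and limits the weight of the point. Baseline measurement helps less for adherence, which is recorded from exercise sessions during the trial, and it does not deal with a source that affects change over time.

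**Conclusion.** The point holds as a modest and inexpensive improvement. Recruitment source is tied to fall severity by design, yet the article names it neither in the randomization nor in the ANOVA. If allocation is not stratified, at least one intervention arm differs from control by 25 points or more in source mix with probability about 21% to 36%. For one given pair of arms of 16 it is about 16% to 22%. These figures rest on the assumed source splits and on the 25-point threshold. The consequence is lost precision and harder interpretation of the pilot estimates, in proportion to how strongly source predicts the outcome. The documents do not quantify that link. The comparison is not biased in expectation.

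**What to change.** 1. Include recruitment source (falls prevention programme or sheltered housing) as a term in the primary and secondary analyses. It is known for every participant, so this can be done whatever the allocation scheme was, and it should be fixed before the outcome data are examined.
2. State whether allocation is stratified by source. If it is not, use permuted blocks within each source, for example with random sizes 3 and 6, for the allocations still to be made. The Trial status section has recruitment running from October 2012 to July 2013, so this may cover only part of the sample; the analysis term covers all of it.

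The cost is a new computer list, one degree of freedom and slightly more predictable allocation, which random block sizes limit.

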**Figure 1 F1:**
[figure not shown]
Flow diagram of trial design showing the three arms of the study (control, visualizations and multimodal games).

### Home-based falls rehabilitation

Home rehabilitation for falls includes specially tailored exercises designed to improve muscle strength and balance in the lower limbs, as well as core stability. This is achieved by challenging important muscles, as well as training joints through their normal range of movement for a set number of repetitions (or for a certain amount of time). For falls rehabilitation, these exercises are usually provided to older adults in the form of instructional booklets or videos. Each exercise session involving the use of these tools is expected to last for 30 to 45 minutes.

### Intervention

The Age UK falls rehabilitation booklet
[15] is commonly used in falls services in the UK for home-based exercise and will be used as standard care in this study. This booklet contains a warm-up, a cool-down and ten exercises in total, comprising five balance and five strength exercises. Following recruitment, the participants will be allocated to one of three interventions in this study, namely control, visualization, or multimodal games.

Control: the control group will receive the standard home-based rehabilitation care for falls prevention provided by the NHS Greater Glasgow and Clyde Falls Service. This includes the Age UK booklet previously mentioned.

Visualization: the participants in this group will receive visualizations of their movement during home rehabilitation in addition to standard care. The visualizations will serve three main purposes as follows: to 1) present the rehabilitation exercises to the participants using an animated mannequin that will demonstrate the correct range and speed of motion required for each exercise. Instructions on how to perform these exercises will also be shown; 2) show the users real-time feedback of their movements as they perform their exercises and provide a summary of their performance during the process, and 3) provide lay information on the principles behind strength and balance exercises, and to explain the role of these exercises in the prevention of falls.

The proposed visualization tool will be able to execute these functions in a variety of ways. First, through the use of a digital mannequin, the users will receive information on the ideal way to perform strength and balance exercises. The goal of falls rehabilitation is to perform exercises using a recommended (by a physiotherapist) range and speed of motion. By performing these movements using affected limbs, strength can be restored, or acquired, in the relevant limb/body segment(s). We have collaborated with leading falls experts and physiotherapists in the local falls service on the definition and incorporation of these optimal movements into our visualization software. Second, the users will have the ability to visualize their own movements on a screen, using input from body-worn inertial sensors. This is to enable them to compare their movements with the recommended movement. Third, the visualization tool will provide users with a summary of their movement performance, and advise them on how to avoid and correct any incorrect/compensatory movements that occur during home exercise sessions (Figure
2).

**Figure 2 F2:**
[figure not shown]
Concept design of visualizations showing users when they performed exercises incorrectly.

Multimodal games: participants in this group will receive multimodal games in addition to the standard care during the trial. Multimodal games can be used to encourage users to exercise, as the use of games provides a sense of engagement and distracts the user from the essential but repetitive nature of rehabilitation exercises. The games will serve two main functions: to 1) provide the users with a more interactive and enjoyable way to perform home exercise, and 2) inform the users on their performance and progress during rehabilitation by tracking game scores, achievements and correct repetitions of movements during exercise.

To ensure that the games satisfy the requirements necessary for effective falls rehabilitation, their main mechanics will be based on movements required to successfully perform the exercises in the Age UK booklet. The users will be able to perform their exercises by interacting with the games through full body interaction, using inertial sensors strapped to their arms and legs.

When it comes to designing games and other multimodal activities for rehabilitation, we believe that it is not enough for young designers to decide what older adults will consider an enjoyable experience. Previous studies in this field have recognized the need to evaluate such tools with older adults, especially in stroke rehabilitation
[16], but have stopped short of actually encouraging the seniors to design their own tools. This study aims to include users in the design of games in order to address many of the concerns that they may have regarding the use and interaction with the tools. Figure
3 shows one of the games co-designed with older adults at a user workshop conducted as part of this research. The base mechanics of this game (which involved users having to sit and stand to control the flight of a bird in order to collect letters in the game) were suggested by seniors at a workshop, where they worked in groups to design various games for the different falls exercises
[8]. Pre-trial pilot studies with fallers will also ensure that the games are designed and modified to a suitable specification for use in the trial.

